### Outcomes

#### Primary Outcome Measures

The primary outcome of the study was psychological adjustment for cancer, measured 6 months after pulmonary resection. The Korean version of the Mini-Mental Adjustment to Cancer (Mini-MAC) was used to assess survivors’ psychological adjustments to cancer. The Mini-MAC is a 29-item scale scored on a 4-point Likert scale (1=definitely does not apply to me and 4=definitely applies to me) previously validated in Korea [24,25]. The Korean-validated scale consists of the following 4 dimensions: helpless-hopeless (8 items), anxious preoccupation (8 items), cognitive avoidance (4 items), and positive attitude (9 items). The positive attitude dimension contained items identical to those of fighting spirit and fatality from the original Mini-MAC. The total score is the sum of all dimension scores, with higher scores indicating a stronger use of coping strategies. Permission to use the Mini-MAC was obtained from the International Psycho-Oncology Society on May 19, 2021.

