### Data Collection

The clinical trial procedure and intervention are outlined in Figure 1, with the outcomes assessed at baseline (T0), 1 month (T1), 6 months (T2), and 1 year (T3) postoperatively. Baseline data will be collected before surgery and immediately after enrollment. To enhance participant retention and adherence, individuals in both groups received a small token of appreciation upon completion of each of the 3 postoperative follow-up assessments (T1-T3). For participants who discontinued or deviated from the intervention protocols, the data collected up to the point of departure were included in the intention-to-treat analysis to maintain the robustness of the trial results and minimize the impact of attrition bias. The data obtained from self-administered questionnaires were coded and stored in password-encrypted Microsoft Excel (Microsoft Corp) files on a secure computer server. The specific variables measured at each time point are listed in Figure 2.

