### Statistical Analysis

To assess the effectiveness of LC^3^P, we compared the outcomes between the intervention and control groups at multiple time points. The primary analyses involved independent sample 2-tailed *t* tests for continuous variables and chi-square tests for categorical variables to compare baseline characteristics and outcomes between the 2 groups at each follow-up. To account for repeated measures within participants over time and potential within-subject correlations, a mixed-model repeated-measures analysis was used.

In addition to primary analyses, sensitivity analyses probed the robustness of the trial findings under different assumptions regarding missing data and the effects of protocol adherence on treatment outcomes. This included intention-to-treat and per-protocol analyses. Moreover, subgroup analyses were conducted to examine the variability in treatment effects across different patient characteristics such as age, cancer stage, and the presence of comorbid conditions. All tests were 2-tailed, with a significance level of *P*<.05. To address multiple testing concerns, particularly with numerous secondary outcomes, we used Bonferroni correction or other suitable adjustments to preserve the overall type I error rate. All statistical analyses were conducted using STATA/MP (version 16.0; StataCorp).

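### The analysis labelled primary is t tests at every follow-up, the mixed model has no rank, and nothing says which result decides at 6 months

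*Protocol article*

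**What the plan says.** All references are to the protocol article.

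- **Primary Outcome Measures** fixes one time point: "The primary outcome of the study was psychological adjustment for cancer, measured 6 months after pulmonary resection".
- **Statistical Analysis** gives the label to t tests: "The primary analyses involved independent sample 2-tailed" t tests for continuous variables, with chi-square tests for categorical ones, "to compare baseline characteristics and outcomes between the 2 groups at each follow-up".
- **Data Collection** shows which visits these are, "with the outcomes assessed at baseline (T0), 1 month (T1), 6 months (T2), and 1 year (T3) postoperatively". There are three follow-ups after baseline.
- **Statistical Analysis** continues: "To account for repeated measures within participants over time and potential within-subject correlations, a mixed-model repeated-measures analysis was used". No rank, outcome or contrast is attached to this model.
- **Data Collection** says of participants who discontinue or deviate that "the data collected up to the point of departure were included in the intention-to-treat analysis", and gives the purpose: "to maintain the robustness of the trial results and minimize the impact of attrition bias".
- **Statistical Analysis** places that analysis elsewhere. After introducing sensitivity analyses as additional to the primary ones, it says: "This included intention-to-treat and per-protocol analyses".
- The same section sets a two-sided 0.05 level. It also mentions Bonferroni or another suitable correction, aimed particularly at the secondary outcomes.

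**The concern.** The outcome is specific and the analysis is not. At T2 the plan yields at least two p-values for the same question: one from a t test on those with a T2 score, and one from a mixed model. They can fall on opposite sides of 0.05, and the text does not say which counts.

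The method that carries the primary label is also the weaker one. It ignores the T0 score, and it cannot use T0 or T1 scores from someone with no T2 score unless those values are imputed. Data Collection relies on exactly those partial data to limit attrition bias, but ties them to an intention-to-treat analysis that Statistical Analysis lists under sensitivity. The protection described in one section is thus not visibly part of the analysis named primary in the other.

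At stake are the type I error of the one confirmatory claim, possible bias from dropout, and some power.

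**Working it through.** **1. What the sample size assumes.** Inputs from Sample Size Calculation: effect size 0.25, 252 per group, 16% dropout. Power is not stated; 80% reproduces the figure.

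n = 2(1.960 + 0.842)² / 0.25² = 2 × 7.85 / 0.0625 ≈ 251.2, so 252 per group. Then 252 / 0.84 = 300. Both stated figures reproduce. They correspond to one two-sided 0.05 t test at one visit. Bonferroni over three visits (alpha 0.0167) would need 336 per group, or 336 / 0.84 = 400 with dropout.

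**2. Choosing between two analyses at T2.** With no effect and no systematic T0 difference between groups, the t statistic and the baseline-adjusted statistic on the same people have correlation √(1 − ρ²), where ρ is the T0–T2 correlation. The documents give no ρ, so a range is shown.

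| Assumed ρ | Correlation of the two statistics | P(at least one p < 0.05) |
|---|---|---|
| 0.3 | 0.954 | 6.4% |
| 0.5 | 0.866 | 7.4% |
| 0.7 | 0.714 | 8.3% |

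If the second analysis also uses T1, as a mixed model does, simulation with 16% random dropout gives 7.8% (ρ = 0.5) and 8.6% (ρ = 0.7).

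**3. Three visits, conditional.** If success at any of T1, T2 or T3 counted, each at an unadjusted 0.05, the family-wise error would be 13.1%, 12.5%, 11.8% and 10.9% at assumed between-visit correlations of 0.4, 0.5, 0.6 and 0.7. With independent tests it would be 1 − 0.95³ = 14.3%.

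**4. Who is left out of a T2 t test.** Enrolment was 441 and 350 (Results). At 16% dropout, 441 × 0.16 ≈ 71 controls and 350 × 0.16 = 56 intervention participants have no T2 score, leaving about 370 and 294.

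**5. Bias from dropout.** Assume no true effect, a T1–T2 correlation of r = 0.6, 16% dropout in each group, random dropout in controls, and dropout in the intervention group that rises by b log-odds per SD of lower T1 score. The shift in the T2 mean of those retained is

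bias = r × b × E[p(1 − p)] / 0.84,

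where p is the individual dropout probability.

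| b | E[p(1 − p)] | Bias (SD) | Standard error | Rejection at 0.05 |
|---|---|---|---|---|
| 0.5 | 0.130 | 0.6 × 0.5 × 0.130 / 0.84 = 0.046 | 0.078 | 9% |
| 1.1 | 0.115 | 0.6 × 1.1 × 0.115 / 0.84 ≈ 0.09 | 0.077 | 22% |

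If both groups share the mechanism and rate, the shifts cancel and the bias is 0. An estimator that uses T0 and T1 has bias of about 0 in simulation, because here dropout depends only on the observed T1 score.

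**6. Power.** For an effect of 0.25 SD at 370 and 294, the standard error is √(1/370.44 + 1/294) = 0.0781. Then 0.25 / 0.0781 − 1.96 = 1.24, which is 89.3% power for the t test. Baseline adjustment multiplies the standard error by √(1 − ρ²), giving 91.9%, 95.9% and 99.4% at ρ = 0.3, 0.5 and 0.7.

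**The case against.** **The time point is fixed.** A reader might infer that the plan leaves T1, T2 and T3 all open for the primary claim. The documents do not support that. The Abstract, the Introduction, Primary Outcome Measures and Sample Size Calculation all specify 6 months, and the sample size matches a single test. The sentence on each follow-up also covers baseline characteristics and chi-square tests, so it can be read as a general description of comparisons. This stands. What remains is that the sentence carrying the primary label is not restricted to T2.

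**Multiplicity is mentioned.** A reader might take 11%–13% as the trial's error rate. That needs a rule that any visit wins, without adjustment. The plan states no such rule and mentions Bonferroni or an alternative. This stands too, although the correction is not tied to visits and does not choose between methods. The 400 per group in step 1 equals the enrolment aim, but the article justifies that aim by robustness, subgroups and smaller effects, not by three visits.

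**The mixed model may itself be primary.** It sits in the same paragraph as the t tests, and the next paragraph starts from analyses additional to the primary ones. On that reading, partial data already enter a primary analysis. That is a fair reading, but then there are two primary analyses and still no rule between them.

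**No complete-case rule is stated.** This is correct. The loss of partial data follows from how a t test works. The plan does promise sensitivity analyses under different missing-data assumptions, and a fuller plan may specify imputation. Even so, the article has already assigned the primary label, and a later document would have to revise it.

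**The bias depends on the scenario.** This is also correct. The upper figure needs one-sided dropout with an odds ratio near 3 per SD.

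**Conclusion.** The point holds as a defect in how the primary analysis is fixed. T2 is settled; the deciding method at T2 is not. The method named first as primary cannot, without imputation, use the partial data that Data Collection counts on.

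- **Type I error from the choice of method at T2:** about 6%–8% instead of 5%, for an assumed T0–T2 correlation of 0.3–0.7 and no systematic T0 difference between groups.
- **Attrition bias in the t test:** from 0 to about 0.05–0.09 SD, with 9%–22% rejection under no effect, under the assumptions in step 5. Correlation, mechanism and strength are assumed; only the 16% is from the article. These figures show a risk and do not predict a result.
- **Error from multiple visits:** about 11%–13%, conditional on a success rule the plan does not contain. It should not be quoted as the trial's error rate.

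Confidence is high on the unclear ranking and much lower on the size of any bias. This should be corrected, and it can be in time, because Results says the analyses are still to be performed.

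**What to change.** Before any outcome analysis, amend Statistical Analysis as follows:

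1. The single primary test is the T2 group contrast in Mini-MAC from the planned mixed model (group, visit, group-by-visit, T0 score), using all enrolled participants with any data, at two-sided 0.05.
2. The T1 and T3 contrasts are secondary, under the multiplicity adjustment already mentioned, with the method named.
3. The t tests at each visit are descriptive.
4. The data set in Data Collection that includes data up to departure is the one for this primary test, and is no longer listed only under sensitivity.

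State also whether T0 enters as a covariate or as the first repeated measurement. A person with only a T0 score contributes only in the second form.

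The cost is a few sentences, slightly more modelling and no new data. The model relies on data being missing at random, which the planned missing-data sensitivity analyses can probe. Adjustment for confounding between the non-randomised groups is a separate matter that this change does not settle.

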#### Secondary Outcome Measures

The secondary outcomes were unmet informational needs, quality of life, distress, and symptoms. Unmet informational needs were assessed using the information needs scale (3 items) from the Korean version of the Cancer Survivors’ Unmet Needs scale [26,27]. Health-related quality of life is measured using the Korean version of the European Organisation for Research and Treatment of Cancer Quality of Life Questionnaire—Core 30 [28]. Distress was assessed using the National Comprehensive Cancer Network Guidelines for Distress Management (version 2.2021) [29]. The European Organisation for Research and Treatment of Cancer Quality of Life Questionnaire—Lung Cancer 13 [30], the Chronic Obstructive Pulmonary Disease Assessment Test [31,32], and the modified Medical Research Council dyspnea scale [33] are used to assess the presence and severity of symptoms related to lung cancer.

The Korean version of the International Physical Activity Questionnaire-Short Form is used to identify participants’ levels of physical activity [34]. Depending on the level of activity derived from the questionnaire, patients were categorized into high, moderate, or low groups. The Hospital Anxiety and Depression Scale is a measure of depressive mood [35]. The components of each intervention and the hypothesized effects on the primary and secondary outcomes are shown in Figure S3 in Multimedia Appendix 1.

Sociodemographic variables such as age, sex, and level of education were acquired directly from the participants via self-reported questionnaires. Clinical characteristics, such as cancer stage, type of treatment, and postsurgical complications, were obtained from electronic medical records.

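### Secondary-outcome multiplicity is worded too openly for its error-control claim to be checked, and Holm's procedure would be a free improvement on Bonferroni, the only method named

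*Protocol article*

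**What the plan says.** The Statistical Analysis section sets the level for every test: "All tests were 2-tailed, with a significance level of" P<.05. It then turns to multiple testing, with the secondary outcomes chiefly in mind, and states "we used Bonferroni correction or other suitable adjustments to preserve the overall type I error rate". Bonferroni is the only procedure named. No divisor is given.

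The Secondary Outcome Measures section opens with four constructs: "The secondary outcomes were unmet informational needs, quality of life, distress, and symptoms". Under the same heading it describes eight instruments:

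- one each for information needs, quality of life and distress;
- three symptom scales (QLQ-LC13, CAT and mMRC), which "are used to assess the presence and severity of symptoms related to lung cancer";
- one for physical activity: "The Korean version of the International Physical Activity Questionnaire-Short Form is used to identify participants’ levels of physical activity";
- one for mood: "The Hospital Anxiety and Depression Scale is a measure of depressive mood".

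Physical activity and depressive mood are not among the opening four.

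On timing, the Statistical Analysis section says "we compared the outcomes between the intervention and control groups at multiple time points", with tests to "compare baseline characteristics and outcomes between the 2 groups at each follow-up". The Data Collection section gives three postoperative assessments (1 month, 6 months and 1 year).

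**The concern.** Preserving the overall type I error rate is a property of a particular procedure applied to a particular set of tests. The sentence claims the property but leaves the procedure open, and the outcome section gives an opening list that is shorter than what follows it. A reader of the eventual results could not tell from this article which threshold a secondary P value had to meet.

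The choice of method also matters. Some procedures that might be thought suitable do not control familywise error. The one that is named, Bonferroni, does control it, but gives away power that Holm's procedure keeps at no cost. Only the secondary claims are at stake. The primary outcome is one measure at one time point.

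**Working it through.** **Inputs.** Two-sided 0.05 (Statistical Analysis). Effect size 0.25, 252 per group, 16% dropout and about 300 per group (Sample Size Calculation). Enrolled: 441 control and 350 intervention (Results). Assumed, because the article does not say: 0.25 is a standardised difference; planned power is 80%; the 16% dropout applies to the enrolled numbers; and the same 0.25 holds for each truly affected secondary outcome.

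**The plan's own figure.** n per group = 2(1.960 + 0.842)² / 0.25² = 2 × 7.85 / 0.0625 ≈ 251.2, so 252. Then 252 / 0.84 = 300. Both figures are reproduced, and nothing below alters them.

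**Possible families.** The Bonferroni level is 0.05/m:

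| m | How it arises | Level per test | Power at d = 0.25 |
|---|---|---|---|
| 4 | opening constructs | 0.0125 | 0.76 |
| 6 | four constructs plus physical activity and mood | 0.0083 | 0.71 |
| 8 | instruments | 0.00625 | 0.68 |
| 24 | eight instruments × three visits | 0.0021 | 0.55 |

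The last row is an upper case. It applies only if every instrument is tested at every visit, and the schedule figure is not shown.

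Power uses the normal approximation. Evaluable numbers are 441 × 0.84 ≈ 370 and 350 × 0.84 = 294. The standard error of a standardised difference is √(1/370 + 1/294) ≈ 0.078, and 0.25 / 0.078 ≈ 3.20. For m = 8 the critical value is 2.73, so power = Φ(3.20 − 2.73) ≈ 0.68.

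**Does Bonferroni control the error rate?** Yes, when the divisor equals the number of tests. In 200,000 simulated trials with no true effects, familywise error was 0.041 to 0.049 (four or eight endpoints, correlation 0 or 0.5).

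**Would every alternative control it?** No. Under Benjamini–Hochberg, a false-discovery-rate method, with four of eight effects real, simulated familywise error was 0.079 (correlation 0.5) to 0.105 (correlation 0). The protocol does not say that it would use that method. The example shows only that the open wording does not secure the property by itself.

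**Holm against Bonferroni, same family.** Holm orders the P values and compares the smallest with 0.05/m, the next with 0.05/(m − 1), and so on, stopping at the first failure. For m = 8 the thresholds are 0.00625, 0.00714, 0.00833, 0.01, 0.0125, 0.0167, 0.025 and 0.05. Each is at least 0.05/8, so every Bonferroni rejection is also a Holm rejection. Holm needs no assumption about correlation.

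Average power per truly affected endpoint, from the same simulations (correlation 0 to 0.5):

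| Endpoints | Real effects | Bonferroni | Holm |
|---|---|---|---|
| 8 | 4 | 0.68 | 0.71–0.72 |
| 8 | 8 | 0.68 | 0.79–0.82 |
| 4 | 2 | 0.76 | 0.78–0.79 |
| 4 | 4 | 0.76 | 0.84–0.86 |

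The largest simulated familywise error for Holm was 0.049.

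**The case against.** The strongest reply is that this is a condensed article. It refers readers to a full protocol on the trial registry, and an analysis plan may exist. The exact procedure, divisor and endpoint list are details that such a document usually holds, so their absence here is not a fault. That stands. What remains is the wording of a sentence that claims a property, and an opening list that does not match its own section.

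Second, the document states no count of secondary outcomes. Three of the eight instruments sit inside the listed symptoms construct, so four constructs and several instruments do not contradict each other. That also stands. Only physical activity and depressive mood fall outside the opening list.

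Third, Bonferroni is valid and the current wording already permits Holm. Correct: recommending Holm improves efficiency and does not repair an error. The larger gains also need all the effects to be real, and 0.25 is stated only for the primary outcome. Physical activity is categorised as high, moderate or low, so a standardised mean difference does not describe it, although Holm can still use its P value.

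A reader might go further and infer that error control fails. Dividing by 4 while making 8 or 24 independent tests would give 1 − (1 − 0.0125)⁸ ≈ 9.6% or 1 − (1 − 0.0125)²⁴ ≈ 26%. No passage states or implies such a mismatch, so these are not consequences of the plan. Nor do the documents show a method picked after results were seen. The Results section places all analyses after study completion, and the Limitations section reports no change in analysis methods after the initial ethics approval.

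**Conclusion.** The point holds in a limited form. Preservation of the overall type I error rate cannot be verified from the article, but it is not shown to fail. The only method named is uniformly less powerful than Holm's procedure, which gives the same guarantee. With eight endpoints the gain is about 3 to 4 percentage points of average power if half the effects are real, and about 11 to 14 points if all are.

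These sizes rest on the assumed effect of 0.25, 16% dropout, and correlations between 0 and 0.5. That Holm never has less power than Bonferroni rests on none of them. The primary outcome and the sample size are unaffected.

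**What to change.** In the Statistical Analysis section, replace Bonferroni and the unnamed alternatives with Holm's step-down procedure at two-sided 0.05 over the listed secondary outcomes. In the Secondary Outcome Measures section, make the opening list agree with what is described there: physical activity and depressive mood are either named as members of the family or labelled exploratory.

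The cost is two edits to the text. There are no new data, no change to the tests themselves and no loss of power against Bonferroni over the same family.

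Two further steps are optional design choices and are not required. One is to test the secondary outcomes only if the Mini-MAC result at 6 months is significant. The other is to confine the family to 6 months. The first can cost more power than Holm gains: with primary power of about 0.89, four of eight effects real and independent outcomes, 0.89 × 0.72 ≈ 0.64, below the 0.68 of plain Bonferroni. It would also bar every secondary claim after a null primary result. The second would make the 1-month and 1-year secondary comparisons descriptive.

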### Ethical Considerations

This study was approved by the IRB of the SMC (SMC 2021-08-071). If any critical amendments, including but not limited to the eligibility criteria, outcomes, and analyses, become necessary in the future, modifications to the protocol will be shared with all relevant parties, including all investigators, the IRB committee, and the trial registry. A trained research assistant initiated contact with potential participants after screening for eligibility. Written informed consent forms were obtained after the purpose, procedure, and potential harm of participating in the study were explained. Informed consent was obtained from each patient before enrollment in the study. Personal data such as sociodemographic information, clinical characteristics, and outcomes measured at each visit were coded with a unique study identification number in password-encrypted Microsoft Excel files stored on a secure computer server to prevent unauthorized access. Hard copies of the questionnaire were retained for a decade after the completion of the study. Both the primary investigator and coinvestigators had access to the final data set without any contractual regulations.

